### **13. Quality Control and Quality Assurance**

#### **13.1 Responsibilities of investigators**

The Investigator(s) undertake(s) to perform the Clinical Trial in accordance with this Clinical Trial Protocol, ICH guidelines for Good Clinical Practice and the applicable regulatory requirements.

The Investigator is required to ensure compliance with all procedures required by the Clinical Trial Protocol and with all study procedures provided by the Sponsor (including security rules). The Investigator agrees to provide reliable data and all information requested by the Clinical Trial Protocol (with the help of the Case Report Form [CRF], Discrepancy Resolution Form [DRF] or other appropriate instrument) in an accurate and legible manner according to the instructions provided and to ensure direct access to source documents by Sponsor representatives.

The Investigator may appoint such other individuals as he/she may deem appropriate as Sub-Investigators to assist in the conduct of the Clinical Trial in accordance with the Clinical Trial Protocol. All Sub-Investigators shall be appointed and listed in a timely manner. The Sub-Investigators will be supervised by and under the responsibility of the Investigator. The Investigator will provide them with a copy of the Clinical Trial Protocol and all necessary information. The sponsors shall be responsible for the health authority, taking any possible methods to ensure the appropriate management of the clinical study, these methods including Ethics, compliance of the study plan, the integrity and validity of the clinical data.

#### **13.2 Study Monitoring**

The main responsibility of the Monitoring Committee is to assist the investigators and sponsors in the all aspects of the clinical study in a highly ethics, scientific, professional and normalization manner. According to the ICH guidelines for Good Clinical Practice, the Monitoring Team must check the Case Report Form entries against the source documents.

At regular intervals during the Clinical Trial, the site will be contacted, through monitoring visits, letters or telephone calls, by a representative of the Monitoring Team to review study progress, investigator and patient compliance with Clinical Trial Protocol requirements and any emergent problems. During these monitoring visits, the following but not exhaustive list of points will be scrutinized with the investigator: patient informed consent, patient recruitment and follow-up, Serious Adverse Event documentation and reporting, Investigational Product allocation, patient compliance with the Clinical Trial Protocol and the Investigational Product regimen, concomitant therapy use and quality of data.

#### **14. Data Preservation**

All CRFs and image data should be delivered to data management center by the inspector and should be checked and received by the directors of the data storage center. All CRFs which should be kept in this center should be completed entirely in a neat, legible manner to ensure accurate interpretation of data. After the data entry was completed, the CRFS should be saved by the research center.

## 15. Safety Monitoring of Data

Corresponding data security monitoring plan will be developed based on the risk of the Clinical Trial. All adverse events will be recorded in detail, properly handled and tracked until events are resolved properly or the condition becomes stable. Serious adverse events and other events should be reported to the ethics committee, competent authorities, sponsors, and drug supervision and management departments according to applicable regulations. The main investigators will regularly review all adverse events. Researchers meeting will be held to assess the risks and benefits of the study if necessary. For studies that exceeds the minimum risk, independent data monitor will be assigned to monitor the research data. An independent data safety inspection committee will be established for high-risk research to monitor the accumulated safety data and effectiveness, making recommendations on whether to proceed with the proposal or not.

During the clinical trial, the subject's data should be collected anonymously on the CRFs. Subjects can only be identified as the subject number and the “pinyin” abbreviation of name. Due to security or administrative instructions, those who accidentally knows the identity of the subject should be responsible for confidentiality along with the investigators. Informed Consent Forms allow authorized sponsors, ethical committees, and authoritative agencies to directly access relevant original data on CRFs (such as patient medical records, appointment records, original laboratory records, etc.). The above personnel should follow the professional secrecy regulations and must keep confidential data of patients’ personally identifiable information or medical information.

## 16. Statistical Processing

### Main null hypothesis

- 1) In patients with acute mild ischemic stroke or high-risk TIA patients attributed to extracranial or intracranial atherosclerosis treated within 72 hours of ictus, there is no difference in the risk of a new stroke within 90 days between subjects with intensive antiplatelet therapy and those with standard antiplatelet therapy.
- 2) In patients with acute mild ischemic stroke or high-risk TIA patients attributed to extracranial or intracranial atherosclerosis treated within 72 hours of ictus, there is no difference in the risk of a new stroke within 90 days between subjects with immediate intensive statin therapy (atorvastatin 80mg/d) and delayed intensive statin therapy (atorvastatin 40mg/d).
- 3) In patients with acute mild ischemic stroke or high-risk TIA patients attributed to extracranial or intracranial atherosclerosis treated within 72 hours of ictus, there is no difference in the risk of a new stroke within 90 days between subjects with intensive antiplatelet combined with immediate intensive statin therapy (atorvastatin 80mg/d) and standard antiplatelet combined with delayed intensive statin therapy (atorvastatin 40mg/d).

### 16.1 Estimate Sample Size

The minimal sample size for the trial is determined by the necessity that a clinically meaningful difference in effectiveness between treatment and control groups has to be detected. Based on previous studies, the risk of new stroke during 90 days is presumed to be 11.5% in the group with standard antiplatelet therapy (with half delayed intensive statin therapy and half early high-intensity statin therapy) and 11.5% in the delayed intensive statin therapy group (with half standard antiplatelet therapy and half dual antiplatelet therapy) and 13% in the group with standard antiplatelet therapy plus delayed intensive statin therapy, intensive antiplatelet therapy and immediate intensive statin therapy can reduce this risk by 22%, and the effects of intensive antiplatelet and lipid lowering therapy will be similar and additive. With a sample size of 6100 subjects, a two-sided  $\alpha$  of 0.05 and 5% loss to follow up, we will have 97% power to detect that the risk is decreased by 35% in the group with dual antiplatelet therapy plus immediate intensive statin therapy compared to standard antiplatelet therapy plus delayed intensive therapy, and 80% power to detect that the risk is reduced by 20% by intensive antiplatelet therapy compared to standard antiplatelet therapy, and immediate intensive statin compared to delayed intensive statin therapy, respectively.

**Table1 For different risk rates (12% to 14%) of the results in the control group, the sample size required for observing intensive antiplatelet combining intensive statin therapy**

| Power | A single set of sample size (no expulsion) | A single set of sample size (5% expulsion rate) | Four groups of sample size | The stroke recurrence rate in treatment group | The stroke recurrence rate in control group | Relative risk |
|-------|--------------------------------------------|-------------------------------------------------|----------------------------|-----------------------------------------------|---------------------------------------------|---------------|
| 0.966 | 1448                                       | 1525                                            | 6100                       | 0.078                                         | 0.120                                       | 0.65          |

|       |      |      |      |       |       |      |
|-------|------|------|------|-------|-------|------|
| 0.975 | 1448 | 1525 | 6100 | 0.085 | 0.130 | 0.65 |
| 0.985 | 1448 | 1525 | 6100 | 0.091 | 0.140 | 0.65 |
| 0.824 | 1448 | 1525 | 6100 | 0.096 | 0.130 | 0.74 |

**Table2 For different risk rates (12% to 14%) of the results in the control group, the sample size required for the marginal effect analysis of observed intensive antiplatelet combining intensive statin therapy**

| Power | A single set of sample size (no expulsion) | A single set of sample size (5% expulsion rate) | Four groups of sample size | The stroke recurrence rate in treatment group | The stroke recurrence rate in control group | Relative risk |
|-------|--------------------------------------------|-------------------------------------------------|----------------------------|-----------------------------------------------|---------------------------------------------|---------------|
| 0.807 | 2896                                       | 3050                                            | 6100                       | 0.0930                                        | 0.1157                                      | 0.80          |

Explanations of data sources on recurrence risk and the risk of stroke recurrence after treatment:

At present, evidence in early risks of recurrent stroke in high-risk symptomatic intracranial or extracranial artery stenosis patients is still lacking. The data currently available for reference include: a) In the studies of WASID and SAMMPRIS, the recurrence risk of stroke in the medication treatment group with symptomatic intracranial artery stenosis (stenosis rate > 70%) were 21.9% and 12.6% at 1 year, respectively. The recurrence risk of 12.6% at 1 year in SAMMPRIS research was based on the combination of dual anti-platelet therapy, intensive lipid-lowering and blood-pressure-lowering therapy. Therefore, for the recurrence risk of the standard therapy group, 13% was a conservative figure in our study. b) The subgroup study of the CHANCE Trial has revealed a recurrence risk of 12.5% in patients with intracranial arterial stenosis (stenosis rate > 50%) at day 90. In the CHANCE trial, patients with intracranial arterial stenosis associated with multiple infarcts had a recurrent stroke risk of a striking number of 18% at 90 days. Therefore, as the recurrence risk of the standard therapy group, 13% was a conservative data in our study.

Concerning that dual anti-platelet therapy reduces the risk of recurrence of 22%, the CHANCE study confirmed that dual anti-platelet therapy decreased the risk of stroke recurrence by 90 days for TIA and minor stroke by 32% compared with anti-platelet monotherapy. In the CHANCE subgroup, compared with anti-platelet monotherapy, dual anti-platelet therapy decreased the relative risk of stroke recurrence by 21% in patients with intracranial arterial stenosis, and by 50% in patients with multiple cerebral infarctions. Therefore, with dual anti-platelet therapy, our estimate of a relative reduction of 22% in recurrent stroke risk was a conservative data in our study.

Concerning the source of evidence for intensive lipid-lowering combined with intensive antiplatelet therapy decreases the risk of stroke by 35%, a comparative study of SAMMPRIS and WASID before and after pointed out that the risks of recurrent stroke were 21.9% and 12.6% in the intensive drug therapy group and anti-platelet monotherapy group at 1 year, respectively. The risk was decreased by about 50%.

Therefore, the estimated reduction of recurrence risk by 35% was a conservative data in our study.

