#### 16.3.2.2 Efficacy analysis

- 1) Primary outcome:

Survival curves will be estimated for the primary outcome using the Kaplan-Meier procedure and compared using a Cox regression model Wald test, stratified by the opposite arm of the factorial design. First, marginal effects will be compared between intensive and standard antiplatelet therapy, and also between immediate intensive statin therapy (atorvastatin 80mg/d) and delayed intensive statin therapy (atorvastatin 40mg/d). As these are independent comparisons, they have no effect on the type I error rate. For both treatment comparisons, the primary outcome of stroke will be judged to be statistically significant if the treatment test p-value is  $< 0.05$ . Second, if either intensive antiplatelet or immediate intensive statin treatment (atorvastatin 80mg/d) is statistically significant, the effects between combined intensive antiplatelet and immediate intensive statin treatment (atorvastatin 80mg/d) and combined standard antiplatelet and delayed intensive statin treatment (atorvastatin 40mg/d) will be tested. Cox regression model stratified by the opposite arm of the factorial design, will be used in the curative effect assessment and evaluation between the subgroups.

- 2) Secondary outcomes:

- d. Kaplan-Meier curve will be used to simulate the cumulative risk of 90-day follow-up combined with secondary endpoint events such as vascular events, ischemic stroke, TIA, myocardial infarction, vascular death and all-cause death. Cox proportional risk model will be used to calculate HR and the 95% confidence interval and the Log-rank test would be used to evaluate the efficacy;
- e. For ordinal stroke or TIA, ordinal logistic regression will be used to calculate OR and 95% confidence interval. For the poor functional outcome (mRS score 2-6) and early neurological deficits (increase in NIHSS score at 7days) indexes, logistic regression will be used to calculate OR and 95% confidence interval.
- f. The validity of the extreme value would be examined, and the sensitivity analysis would be carried out.

- 3) Safety analysis

The overall of safety assessment is all used test medications and the safety follow-up case should be

recorded at least once. The safety evaluation data includes adverse reactions observed during the trial and changes in laboratory data before and after treatment.

Safety evaluation will be analyzed using safety data set.

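### The power stated for combined therapy versus control in 16.1 and Table 1 ignores the significance gate in 16.3.2.2; under similar effects it is about 95% rather than 97%

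*Supplement*

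**What the plan says.** Groups A (both intensive therapies) and D (neither) are compared under the third main null hypothesis: "there is no difference in the risk of a new stroke within 90 days between subjects with intensive antiplatelet combined" with immediate intensive statin and the double-control group. Section 2.1.3 makes this one of three primary purposes.

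Section 16.1 sets the frame ("With a sample size of 6100 subjects, a two-sided $\alpha$ of 0.05 and 5% loss to follow up") and then says "we will have 97% power to detect that the risk is decreased by 35" per cent in A compared with D. Table 1 supports this with four rows. The main row is "0.975 | 1448 | 1525 | 6100 | 0.085 | 0.130 | 0.65" and the last is "0.824 | 1448 | 1525 | 6100 | 0.096 | 0.130 | 0.74" (power, evaluable and randomised patients per group, total, treated risk, control risk, relative risk). On the single factors, 16.1 assumes that "intensive antiplatelet therapy and immediate intensive statin therapy can reduce this risk by 22" per cent and that "the effects of intensive antiplatelet and lipid lowering therapy will be similar and additive". Table 2 gives each marginal comparison a power of 0.807 with 2896 per arm.

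Section 16.3.2.2 puts the tests in order. The two marginal comparisons come first, each at p < 0.05. Then: "Second, if either intensive antiplatelet or immediate intensive statin treatment (atorvastatin 80mg/d) is statistically significant", A is tested against D. The Summary gives the same order. Neither the text nor the tables of 16.1 mention this condition.

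**The concern.** Under the written procedure, a positive result for A versus D needs two things: the A versus D test must be significant, and so must at least one marginal comparison. Power for the first alone is an upper limit on power for both. When the effect is shared between the factors, each marginal contrast is about half the A versus D contrast. The gate can then stay shut although A versus D, had it been tested, would have been significant.

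At stake is whether the power quoted for a primary hypothesis belongs to the procedure that will be run. It also matters whether the 0.74 row, which reads as reassurance that power exceeds 80% for a weaker combined effect, can be relied on.

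**Working it through.** **Inputs.** Two-sided alpha 0.05; 1448 evaluable per group (1448/0.95 is about 1525 randomised); control and treated risks from Table 1; the gate from 16.3.2.2.

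**Step 1: reproduce the plan's figures.** Two-proportion power with pooled variance under the null:

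power = Φ{[(p_D − p_A) − 1.96·s0] / s1}, with s0 = √[2p̄(1−p̄)/n], s1 = √{[p_A(1−p_A) + p_D(1−p_D)]/n}.

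- Main row: p̄ = 0.1075, s0 = 0.01151, s1 = 0.01148; (0.045 − 0.02256)/0.01148 = 1.954; Φ = 0.9747 (stated 0.975).
- Last row: p̄ = 0.113, s0 = 0.01177, s1 = 0.01175; (0.034 − 0.02306)/0.01175 = 0.931; Φ = 0.8241 (stated 0.824).
- The 12% and 14% rows give 0.9663 and 0.9851 (stated 0.966 and 0.985). Table 2 gives 0.8068 (stated 0.807).

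Table 1 therefore contains no allowance for the gate.

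**Step 2: risks in B and C.** The gate depends on these.

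- Equal split on the risk scale: B = C = (p_A + p_D)/2, which is 10.75% in the main row and 11.3% in the last.
- Main row, from the plan's own figures: a 22% reduction from 13% is 10.14%. Table 2 agrees: (13 + 10.14)/2 = 11.57, and 9.30 = (10.14 + 8.46)/2, so A = 8.46%.
- Last row: the documents give no B or C risks, so a range is shown.

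**Step 3: gated power.** This is P(A versus D significant and at least one marginal test significant), from binomial simulation of the four groups with 1,000,000 trials per line. A versus D uses the pooled z test. The marginal tests are Mantel-Haenszel score tests stratified by the other factor, standing in for the stratified Cox Wald test.

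| A / B / C / D risk (%) | A vs D alone | At least one marginal | Gated |
|---|---|---|---|
| 7.8 / 9.9 / 9.9 / 12 | 0.967 | 0.945 | 0.937 |
| 8.5 / 10.75 / 10.75 / 13 | 0.976 | 0.957 | 0.950 |
| 8.46 / 10.14 / 10.14 / 13 | 0.978 | 0.962 | 0.956 |
| 9.1 / 11.55 / 11.55 / 14 | 0.986 | 0.972 | 0.968 |
| 9.6 / 11.3 / 11.3 / 13 | 0.825 | 0.783 | 0.745 |
| 9.6 / 10.14 / 10.14 / 13 | 0.825 | 0.793 | 0.754 |
| 9.6 / 10.5 / 12.1 / 13 | 0.825 | 0.881 | 0.791 |
| 9.6 / 9.6 / 13 / 13 | 0.825 | 0.984 | 0.824 |

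**Step 4: checks.** In the second line the gate fails in 1 − 0.957 = 4.3% of trials. In 0.976 − 0.950, about 2.5 points, A versus D would have been significant; in the rest it is missed anyway. In the equal-split 0.74 line, 0.825 − 0.745 = 8 points are blocked by the gate alone. A trivariate normal calculation, with correlation about 0.71 between the combined and marginal statistics, gives 0.950 and 0.745 for these two lines. Schoenfeld's formula on expected events gives ungated powers of 0.970, 0.978, 0.987 and 0.830, all within one point of Table 1, so a time-to-event test changes little.

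**The case against.** Quoting the nominal power of each comparison is a common convention, and 16.1 does not claim to give power under the sequential procedure. That is fair as a defence of intent. But the gate is part of the prespecified test, the reader is not told that it was left out, and the figure supports a primary hypothesis.

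A reader might infer that the protocol holds two conflicting testing rules. It does not. The list of null hypotheses and 16.1 state no rule on when A versus D is tested; the only rule is in 16.3.2.2, and the Summary agrees with it. What is missing is an allowance for that rule in the power.

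A reader might also infer that the trial is too small. The documents do not support this: 6100 patients rest on the 80% marginal power, which the gate does not affect, and gated power for the 35% reduction stays well above 80%.

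Nor should the loss be put as a doubled risk of missing the effect. That holds for 5.0% against Table 1's 2.5%. With the Table 2 risks and the 97% in the text, it is 4.4% against 3%.

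Finally, a full 22% effect of each drug would give gated power of 98.7% (multiplicative, A = 7.9%) or 99.8% (additive, A = 7.3%). Those risks do not match the 35% reduction for which 97% is quoted, so they do not rescue that figure.

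**Conclusion.** The point stands as a reporting error in the power statement. The stated 97% and the Table 1 values belong to a stand-alone test that the protocol does not run. Under similar effects of the two factors, the written procedure has about 94%, 95 to 96% and 97% power for the three rows with relative risk 0.65. Against the 97% in the text, the main loss is about 1.5 to 2 points; it changes neither the sample size nor the analysis.

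The 0.74 row needs more care. It falls from above 80% to about 75% if the effects are equal, but 75% is not a fixed property of the design: the value is about 79% with B and C at 10.5% and 12.1%, and about 82% if one factor does all the work. The documents do not say which applies to that row, so only the range of about 75 to 82% is supported.

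The results rest on 1448 evaluable patients per group, the Table 1 risks, and binomial tests in place of the stratified Cox model.

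**What to change.** In 16.1 and Table 1, restate the powers for A versus D as power under the 16.3.2.2 gate: about 94%, 95% and 97% for the rows with control risks of 12%, 13% and 14% and relative risk 0.65, and about 95% in place of 97% in the text. State beside them that the two factors are assumed to have equal effects. Give the 0.74 row as about 75 to 82%, depending on how the effect divides between the factors. The present figures may stay alongside if labelled as the power of the individual comparison before the gate.

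Keep the gate as written; there is no reason to loosen the testing order to protect a power figure. The cost is a few words and one table column, and a slightly less favourable statement. No patients are added and no analysis changes.

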## 16.2 Data collection and record

All requirements of the test program in the CRF table must be provided, and the parts not provided should be explained.

Electronic Data Capture (EDC) System will be used to input the data in CRF. All test protocol requirements in the CRF table must be provided, and the part not provided should be explained. The administrator will check the data and correct the obvious errors. Other errors or missing data in the project will be returned to the research center. The research center will verify the original information and relevant information to answer and correct the data query form. The process of queries, responses and corrections will be completed and recorded through the EDC system.

As for paper-based information such as incident report forms, researchers must fill in the data requested by the test program in black or blue pen in carbonless copies of the case report forms to ensure that the copy is clear and readable. If the information needs to be modified, it should not be altered or overwritten. The correct information should be written beside the original information and signed and dated by the modifier. The inspector will make sure the accuracy and completeness of the case report forms, and guide the researchers to make necessary corrections and supplementary questions.

After receiving the data, the sponsor will carry out computer data analysis, additional requirements may arise, and researchers must answer these requirements by confirming or modifying data. The content of the corrections will be added to the EDC through the investigator.

